**Methods:**

This prospective cohort study will recruit women working in tobacco processing who are nonsmokers and women who do not work for the tobacco industry and are nonsmokers living in a nearby area (unexposed group), with a total of 400 expected participants. The impact of TDE on health, including metabolic syndrome parameters; complete blood count; and cardiovascular, liver, renal, and lung function, will be evaluated in relation to urine cotinine levels. Air quality and chemical substances in the air and leaves will also be analyzed. The data will be subsequently analyzed using appropriate statistical tools.

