#### Bioindicator Sampling

Tobacco leaves are also collected to study the accumulation of airborne pollutants, particularly radionuclides and heavy metals, as bioindicators of environmental exposure.

Figure 3 illustrates the recruitment process for the T-CHARM study. The exposed group consisted of a total population of 2333 women who work in tobacco processing, of whom 1816 met the eligibility criteria following screening. From this eligible pool, a target sample of 200 participants was estimated and recruited. To ensure comparability, the unexposed group—women who were nonsmokers and residents of nearby communities—was also designed to include 200 participants, matched by key demographic and environmental factors. The total cohort size for follow-up is projected to reach 400 participants, with data collection encompassing baseline and longitudinal health metrics. All collected data are subjected to analysis using appropriate statistical tools, as outlined in the study’s analysis plan.

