#### Group Comparisons

Comparative analyses between the exposed and unexposed groups will be performed for respondent characteristics, health examination results, medical history, lung function, and blood and urine parameters. Statistical tests will include Student *t* test for continuous (ratio) variables and Pearson *χ*^2^ test or Fisher exact test for categorical variables, and *P* values <.05 will be considered statistically significant.

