## Results

The T-CHARM study was officially funded in the year 2024, with data collection commencing in July 2024. As of August 2025, the study has successfully enrolled 60 participants in each group—women who are nonsmokers and work in tobacco processing (exposed group) and women who are nonsmokers and community members (unexposed group). Recruitment for an additional 80 participants is currently underway, alongside laboratory analyses for the second phase of baseline data collection. These analyses include biomarker profiling, clinical assessments, socioeconomic status, and environmental exposure measurements. The cohort baseline results are expected to be published by the end of 2025, marking a key milestone in the study’s longitudinal design and setting the foundation for future follow-up waves.

In general, among the 60 women recruited for the exposed group, most of them were obese (n=28, 46.7%) and overweight (n=11, 18.3%), 76.7% (n=46) were of Madurese ethnicity, 53.3% (n=32) had education in elementary school, and 45.0% (n=27) were educated until middle and high school. Their mean age was 40 (range 21-52) years. Compared to the other work in that area, tobacco workers are paid well, with 76.7% (n=46) having an income as high as 875,000 IDR (US $52.50). Another key finding is that all the study participants are nonsmokers but exposed to tobacco dust occupationally, and 57.1% (n=60) reported being passive smokers. Health questionnaire answers showed that 60 people complained of eye problems, 28 had dermatological issues, 5 had respiratory diseases, 11 had cardiovascular disease, 60 had neurological problems, and 37 had reproductive issues.

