### Strengths and Limitations

The goal is to understand how TDE affects health over a person’s lifetime. At enrollment, the T-CHARM study collects demographic and occupational data (eg, current address, job role); lifestyle factors (eg, smoking status, dietary habits); biomarkers of exposure, including urine cotinine and other relevant indicators; and general health assessments, covering cardiovascular, respiratory, hepatic, renal, and metabolic parameters. Follow-up assessments will update exposure metrics and health status periodically, enabling dynamic tracking of disease progression and risk factors [39].

T-CHARM’s major asset is its multisource medical data integration, which includes clinical records from corporate clinics and district health centers; national health insurance data, offering continuity and completeness; and direct input from general practitioners affiliated with the research team, allowing for nuanced clinical insights beyond standard registry linkages. This approach mitigates common limitations in cohort studies, such as recall bias and loss to follow-up from self-reported questionnaires.

While traditional epidemiological studies focus on cancer, respiratory, and cardiovascular diseases, T-CHARM broadens the scope to include neurological disorders, degenerative diseases, and chronic morbidity patterns linked to environmental and occupational exposures. The longitudinal nature of general practitioner data enables detailed tracking of disease onset, progression, and comorbidities—offering a more comprehensive understanding of health trajectories in exposed populations.

Existing biases or weaknesses have been minimized, but as a cohort study, there are some limitations. The limitations include changes in characteristics of participants over time, loss to follow-up, and confounding variables that complicate data analysis due to a lack of randomization. Potential respondents are also sometimes difficult to recruit due to the invasive nature of blood collection. Additionally, biases can arise from knowledge of exposure status, participant dropout, changes in behavior due to participation, and data quality issues in retrospective studies.

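### The abstract asks how health relates to urine cotinine, but no analysis named in the article estimates that relation

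*Protocol article*

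**What the plan says.** - **Question.** The abstract's Methods paragraph lists metabolic, blood count, cardiovascular, liver, renal and lung measures and says that the effect of tobacco dust on them "will be evaluated in relation to urine cotinine levels".
- **Named tests.** Under Group Comparisons: "Comparative analyses between the exposed and unexposed groups will be performed for respondent characteristics, health examination results", and then for further items that include urine parameters. "Statistical tests will include Student *t* test for continuous (ratio) variables"; categorical variables get a Pearson chi-square or Fisher exact test. The threshold is that P "values <.05 will be considered statistically significant".
- **Other named analyses.** Exploratory Subgroup Analyses allows, but does not require, stratification by BMI, age and length of employment. Outlier Management keeps extreme biomarker values unless an analytic error or contamination is confirmed, and examines results both with and without them.
- **Exposure data.** Data Collection Method lists creatinine-adjusted urine cotinine, duration of employment and a questionnaire assessment of tobacco exposure, repeated every 5 years over 20 years. Strengths and Limitations adds: "Follow-up assessments will update exposure metrics and health status periodically".
- **Size.** For exposed women "a target sample of 200 participants was estimated and recruited"; the unexposed group "was also designed to include 200 participants, matched by key demographic and environmental factors". At August 2025 "the study has successfully enrolled 60 participants in each group".

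**The concern.** A two-group test estimates the mean difference between women who do and do not work with tobacco. It does not estimate how lung function, lipids or liver tests change with cotinine, which is the question in the abstract. The job label is a coarse measure of exposure: cotinine can vary widely within each group, and that variation is discarded when only group means are compared. If women leave or enter tobacco work during the 20 years, a baseline label also becomes a poorer measure of exposure over time.

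At stake is whether the published plan commits the study to the estimate that it was set up to give. A secondary matter is the scale of analysis. If an assay is strongly right-skewed, a t test on untransformed values can be much less sensitive than one on logs.

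**Working it through.** **1. Question against named analyses.** The abstract needs cotinine as an exposure, with health measures as the response. Under Group Comparisons cotinine appears only among the urine parameters compared between groups, which makes it a response. Under Exploratory Subgroup Analyses it is not one of the three stratifiers. Length of employment is one, but stratifying on it gives group differences within bands and no exposure-response slope. For unexposed women it is also time in another job. No correlation, regression or model with updated exposure is named.

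**2. Figures available.** The article gives 200 per group but no power, effect size, SD, geometric SD or expected cotinine ratio, so there is no stated figure to reproduce. Everything below assumes a two-sided alpha of 0.05 (sidedness is not stated). For orientation, the difference detectable with 80% power is d = (1.960 + 0.842) × √(2/n):
- n = 200 per group: 2.802 × 0.100 = 0.28 SD
- n = 60 per group: 2.802 × 0.183 = 0.51 SD

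**3. Cost of the group label.** Assumptions: N = 400 in equal groups; the outcome is linear in log cotinine with overall correlation r = 0.14; tobacco work acts on the outcome only through cotinine; the groups' mean log cotinine differs by g within-group SDs.
- Regression on log cotinine: atanh(0.14) × √397 = 0.1409 × 19.92 = 2.81; power = Φ(2.81 − 1.96) = 80%.
- Group t test: the correlation between outcome and group is 0.14 × (g/2)/√(1 + g²/4). At g = 1 this is 0.14 × 0.447 = 0.063; 0.063 × 19.92 = 1.25; power = Φ(1.25 − 1.96) = 24%.

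Simulation (4,000 data sets per row) agrees:

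| g | group t test | regression |
|---|---|---|
| 0 | 5% | 80% |
| 0.5 | 10% | 81% |
| 1 | 25% | 80% |
| 2 | 51% | 81% |
| 3 | 64% | 80% |

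**4. Scale of a skewed assay.** Assumptions: a lognormal assay, 200 per group, the same log-SD in both groups, and a shift set to give 80% power on the log scale, so that log(GMR) = log-SD × 0.28 (GMR = geometric mean ratio). Simulation used 8,000 data sets per row; the log-scale test stayed at 79% to 80% throughout.

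| log-SD | GMR | untransformed t test |
|---|---|---|
| 0.2 | 1.06 | 80% |
| 0.3 | 1.09 | 78% |
| 0.5 | 1.15 | 75% |
| 0.75 | 1.23 | 68% |
| 1.0 | 1.32 | 59% |
| 1.25 | 1.42 | 49% |
| 1.5 | 1.52 | 40% |

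The loss is therefore about 0 to 5 points up to a log-SD of 0.5, about 20 at 1.0 and about 40 at 1.5. With 60 per group the untransformed test has 75%, 60% and 42% at log-SD 0.5, 1.0 and 1.5, which is the same pattern. With no true difference it rejects in 4% to 5% of data sets, so type I error is not inflated.

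**5. What shrinks the loss in step 4** (200 per group, untransformed against log).
- A larger true ratio: at log-SD 1.0, GMR 1.25 gives 42% against 61%, GMR 1.5 gives 88% against 99%, and GMR 2 gives about 100% for both.
- Truncation at the article's 10 ng/mL cutoff, with an assumed unexposed geometric mean of 2 ng/mL: log-SD 1.0 with GMR 1.25 gives 43% against 50%; log-SD 1.5 with GMR 1.5 gives 44% against 55%. Cotinine is screened at eligibility, but the article does not say whether this cutoff is applied there.

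**The case against.** The list of tests is introduced with a word that leaves it open, and the recruitment text refers to an analysis plan that is not shown. That plan may contain a cotinine regression, transformations and rules for values below the detection limit. This stands, and it limits the point to what the article names. It does not remove the mismatch, because the article chose specific tests and none of them answers the question in its abstract.

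A reader might infer more in four ways, none of which the document supports.
- **That a raw-scale t test is prescribed and costs much power.** No scale is stated and transformation is not ruled out. The degree of skew, any larger variance among exposed women and any values below the detection limit are all assumptions.
- **That a few retained outliers will go unnoticed.** The plan examines results with and without them, although that check does not change the scale of analysis.
- **That only the baseline job label is ever used.** Length of employment is an optional stratifier. Cotinine and employment are also not the only exposure data: the questionnaire, particulate and radon measurements are collected too.
- **That a cotinine gradient would be the strongest evidence against confounding.** The Results report 57.1% as passive smokers. Passive smoke can raise cotinine, so a gradient need not isolate tobacco dust.

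The figures in step 4 concern cotinine or another skewed assay as the variable compared. They say nothing about the relation of health to cotinine, for which step 3 is the relevant calculation.

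**Conclusion.** The point holds as a mismatch between the stated question and the named analyses. The article promises health in relation to cotinine and renewed exposure measures, and it names no analysis that uses either as an exposure. It does not follow that the study will never report such an estimate.

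On size, using the group label in place of cotinine can cut power from about 80% to between 10% and 51% when the groups lie 0.5 to 2 within-group SDs apart. This holds if the effect acts through cotinine and r is near 0.14. If tobacco work affects health by routes that cotinine does not capture, the group comparison would do better than this, which is a reason to keep it.

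The scale of the t test is secondary. Its cost runs from nothing to about 40 points over log-SDs of 0.2 to 1.5, and the document does not show where in that range cotinine lies. Assays with little skew lose almost nothing. The change should be made, and it is best made before the baseline analysis.

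**What to change.** In Group Comparisons, or in a new paragraph beside it:

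1. Name an adjusted regression of a short, prespecified list of health outcomes on log urine cotinine, with passive smoking and the other chosen confounders as covariates. Handle creatinine once: either use creatinine-adjusted cotinine or enter creatinine as a covariate, not both.
2. Within exposed women, name a regression of the same outcomes on years of tobacco work.
3. State that both exposures are updated at each wave.
4. Keep the exposed-versus-unexposed comparison alongside.
5. Compare clearly skewed assays such as cotinine on the log scale, reporting geometric mean ratios, or by a rank test. Use left-censored methods only if values fall below the detection limit.
6. If the power loss of an untransformed test is cited, give it as a range with its assumptions.

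The cost is wording only, since cotinine, creatinine and employment duration are already collected. There are three downsides. Skewed assays are reported as ratios instead of mean differences. There are more tests to account for, which is why the outcome list should be short. The cotinine slope will reflect passive smoke as well as tobacco dust, and adjusting for reported passive smoking may not remove this completely.

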#### Exploratory Subgroup Analyses

To minimize bias and explore potential effect modifiers, subgroup analyses may be stratified by BMI, age, and length of employment. These stratified analyses will help identify differential health impacts and refine risk estimates across population subgroups.

## Results

The T-CHARM study was officially funded in the year 2024, with data collection commencing in July 2024. As of August 2025, the study has successfully enrolled 60 participants in each group—women who are nonsmokers and work in tobacco processing (exposed group) and women who are nonsmokers and community members (unexposed group). Recruitment for an additional 80 participants is currently underway, alongside laboratory analyses for the second phase of baseline data collection. These analyses include biomarker profiling, clinical assessments, socioeconomic status, and environmental exposure measurements. The cohort baseline results are expected to be published by the end of 2025, marking a key milestone in the study’s longitudinal design and setting the foundation for future follow-up waves.

In general, among the 60 women recruited for the exposed group, most of them were obese (n=28, 46.7%) and overweight (n=11, 18.3%), 76.7% (n=46) were of Madurese ethnicity, 53.3% (n=32) had education in elementary school, and 45.0% (n=27) were educated until middle and high school. Their mean age was 40 (range 21-52) years. Compared to the other work in that area, tobacco workers are paid well, with 76.7% (n=46) having an income as high as 875,000 IDR (US $52.50). Another key finding is that all the study participants are nonsmokers but exposed to tobacco dust occupationally, and 57.1% (n=60) reported being passive smokers. Health questionnaire answers showed that 60 people complained of eye problems, 28 had dermatological issues, 5 had respiratory diseases, 11 had cardiovascular disease, 60 had neurological problems, and 37 had reproductive issues.

## Discussion

### Study Implications

Most studies related to tobaccosis use active smokers as participants [27,28]. In Indonesia, there has been no research collecting data on tobacco-related diseases, including in the workplace, so the effects of exposure to nicotine-containing tobacco dust on workers’ health are unknown and have not been studied [4]. Problems in this industry are also not easy to solve because they are often related to public welfare, government policy, and sometimes political influence [29]. Previous studies have found significant effects of tobacco dust on tobacco industry workers [4]. Further evaluation is needed to determine the effects of chronic exposure to tobacco dust. This study serves as a baseline for a future cohort study. Further evaluations are expected to determine the effects of tobacco dust, avoiding the biases in cross-sectional studies. This exposure is similar to thirdhand smoking conditions, so the results of this study will benefit those exposed to tobacco at work and through thirdhand smoke in the wider community.

Tobacco leaf sorters play a critical role in determining the appropriate use of tobacco leaves, whether as wrappers or binders, based on their quality. Leaf inspection involves both internal assessments (eg, human sensory evaluation, smoking tests, and chemical analysis) and external examinations (primarily visual inspection) [30]. Workers sort tobacco leaves by evaluating attributes such as quality, size, color, and dryness, requiring sustained attention to fine details over extended periods. This meticulous and repetitive visual task places workers at elevated risk for eye fatigue or asthenopia, particularly in the absence of proper environmental controls and scheduled rest periods [31].

Itching is a common health complaint among new tobacco leaf sorters, often presented as a mild form of contact dermatitis resulting from exposure to nicotine and other chemical residues on the leaves [32,33]. Preventive measures such as the use of personal protective equipment and maintaining proper skin hygiene can significantly reduce the risk of dermatitis [34,35]. However, implementing personal protective equipment—particularly gloves—poses a practical challenge. Sensory assessment of tobacco leaves, which relies heavily on tactile feedback, often requires workers to sort without gloves, limiting the feasibility of full protection.

Tobacco leaf sorters are at risk of developing neurological symptoms such as paresthesia, headaches, and dizziness, which are commonly linked to green tobacco sickness, a form of acute nicotine poisoning caused by transdermal absorption of nicotine from wet tobacco leaves [36,37]. The likelihood of absorption increases significantly when leaves are damp due to dew, rain, or sweat, particularly during early morning or humid working conditions.

Even when individuals are not employed during pregnancy, nausea experienced during pregnancy may be associated with residual effects of prior green tobacco sickness exposure, suggesting potential long-term or latent impacts. To mitigate these risks, it is essential to implement comprehensive preventive strategies aimed at minimizing direct skin contact with tobacco leaves. This includes the use of protective clothing and gloves, although such measures present practical challenges. Gloves, for instance, may interfere with the sensitivity required for leaf sorting, necessitating a careful balance between occupational safety and task performance [38].

### Strengths and Limitations

The goal is to understand how TDE affects health over a person’s lifetime. At enrollment, the T-CHARM study collects demographic and occupational data (eg, current address, job role); lifestyle factors (eg, smoking status, dietary habits); biomarkers of exposure, including urine cotinine and other relevant indicators; and general health assessments, covering cardiovascular, respiratory, hepatic, renal, and metabolic parameters. Follow-up assessments will update exposure metrics and health status periodically, enabling dynamic tracking of disease progression and risk factors [39].

T-CHARM’s major asset is its multisource medical data integration, which includes clinical records from corporate clinics and district health centers; national health insurance data, offering continuity and completeness; and direct input from general practitioners affiliated with the research team, allowing for nuanced clinical insights beyond standard registry linkages. This approach mitigates common limitations in cohort studies, such as recall bias and loss to follow-up from self-reported questionnaires.

While traditional epidemiological studies focus on cancer, respiratory, and cardiovascular diseases, T-CHARM broadens the scope to include neurological disorders, degenerative diseases, and chronic morbidity patterns linked to environmental and occupational exposures. The longitudinal nature of general practitioner data enables detailed tracking of disease onset, progression, and comorbidities—offering a more comprehensive understanding of health trajectories in exposed populations.

Existing biases or weaknesses have been minimized, but as a cohort study, there are some limitations. The limitations include changes in characteristics of participants over time, loss to follow-up, and confounding variables that complicate data analysis due to a lack of randomization. Potential respondents are also sometimes difficult to recruit due to the invasive nature of blood collection. Additionally, biases can arise from knowledge of exposure status, participant dropout, changes in behavior due to participation, and data quality issues in retrospective studies.

### Conclusion

The T-CHARM study is currently in the baseline data collection phase, with plans for long-term follow-up over the next 20 years, contingent on future funding availability. To promote scientific collaboration and maximize the utility of the cohort, external researchers are invited to submit proposals for noncommercial research using the available T-CHARM data. Researchers may also request additional data collection contingent on appropriate funding support. All proposals will be reviewed by the T-CHARM Management Committee to ensure alignment with the study’s objectives and ethical standards. Requests should be directed to the corresponding author, and a data management fee will apply to cover administrative and technical costs associated with data preparation and transfer.

